## Methods: participants, interventions, and outcomes

### Study setting {9}

This study is conducted at two large tertiary hospitals in Negeri Sembilan (Hospital Tuanku Ja’afar) and in Kuala Lumpur (Hospital Kuala Lumpur) that provide surgical treatments to patients diagnosed with breast and colorectal cancers. The screening, recruitment, and baseline data collection are conducted at the surgical outpatient clinics of the hospitals. The patients are followed up at the surgical wards a day prior to surgery and a day prior to discharge from the hospitals. Upon 30 days and 90 days after surgery, the follow-up data collection is carried out at the surgical outpatient clinics of the hospitals.

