### Outcomes of the study {12}

The schedule of enrolment, interventions, and assessments for the study is shown in Table 1. The primary outcomes are body weight, body mass index (BMI), serum albumin, and pre-albumin level. The secondary outcomes include energy and protein intake, muscle and fat mass, handgrip strength, haemoglobin, serum transferrin, high sensitivity C-reactive protein (hs-CRP), interleukin-6 (IL-6), salivary cortisol, sleep quality, length of hospital stay, and postoperative complication rate within 30 and 90 days after surgery. The changes for these parameters will be assessed at a day prior to discharge (V3), 30 days after surgery (V4), and 90 days after surgery (V5) compared to baseline as shown in Table 2.

**Table 2 Tab2:** Outcome parameters’ description

Domain	Specific measurements	Metric and time points for assessment	Method of aggregation
Primary outcomes			
Nutrition status	Body weight, kg	Change from baseline (V1) at1 day prior to discharge (V3); change from 1 day prior to discharge (V3) at 30 days after surgery (V4); change from 1 day prior to discharge (V3) at 90 days after surgery (V5)	Mean
	BMI, kg/m^2^		
	Serum albumin, g/L		
	Serum prealbumin, mg/L		
Secondary outcomes			
Nutrition status	Handgrip strength, kgF	Change from baseline (V1) at 1 day prior to discharge (V3); change from 1 day prior to discharge (V3) at 30 days after surgery (V4); change from 1 day prior to discharge (V3) at 90 days after surgery (V5)	Mean
	Muscle mass, kg		
	Fat mass, kg		
	Serum transferrin, g/L		
	Haemoglobin, g/dL		
Inflammation	High-sensitivity C-reactive Protein (hs-CRP), mg/L		Mean
	Interleukin-6 (IL-6), pg/ml		
	Salivary cortisol, μg/dL		
Dietary intake	Energy intake, kcal/d		Mean
	Protein intake, g/d		
Sleep quality	Pittsburgh Sleep Quality Index (PSQI) score		Median
Postoperative complications	Postoperative complications	Frequency of postoperative complications at discharge (V3), at 30 days after surgery (V4), and 90 days after surgery (V5)	Median
	Length of hospital stay	Number of days of hospitalisation from admission (V1) to 1 day before discharge (V3)	Median

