#### Length of hospital stay

The length of hospital stay is calculated from the day of admission up to 1 day prior to being discharged from the hospital. The information is obtained from patients’ hospital records.

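### Table 2 summarises postoperative complications by a median, which would probably be 0 in every arm if the complication rate is about 30% or less, and it labels hospital admission as V1, the outpatient baseline visit

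*Protocol article*

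**What the plan says.** **Complications.** The Table 2 row (Outcomes of the study {12}) gives the metric as "Frequency of postoperative complications at discharge (V3), at 30 days after surgery (V4), and 90 days after surgery (V5"), and its aggregation column says Median. The paragraph above the table lists the same outcome as a complication rate over the 30- and 90-day periods after surgery. Statistical methods {20a} says that categorical data are presented as counts and percentages. The subsection Postoperative complications under {18a} divides events into minor and major.

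**Length of stay.** The next row of Table 2 reads "Number of days of hospitalisation from admission (V1) to 1 day before discharge (V3"). For the outcomes measured as change, the same table uses V1 for another event: "Change from baseline (V1) at1 day prior to discharge (V3"). Study setting {9} says where that visit takes place: "The screening, recruitment, and baseline data collection are conducted at the surgical outpatient clinics of the hospitals". It puts the first ward contact later: "The patients are followed up at the surgical wards a day prior to surgery and a day prior to discharge from the hospitals". The subsection Length of hospital stay under {18a} has no visit label: "The length of hospital stay is calculated from the day of admission up to 1 day prior to being discharged from the hospital". It takes the information from hospital records.

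**The concern.** The two rows raise different problems.

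For complications, the summary does not suit the outcome. Most patients in an elective surgical series may have no complication, and the median count then says only that fewer than half had one. Arms with clearly different rates can share a median of 0. Table 2, the outcome text and the statistical methods also cannot all be followed as written. The trial is open-label and analysed by unblinded investigators (Who will be blinded {17a}), so the choice should not remain open until results by arm are known.

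For length of stay, one row equates two different days. Someone working from the visit label would start the count at an outpatient visit that, in two arms, precedes 5 to 14 days of preoperative supplementation.

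These two outcomes carry much of the clinical half of the trial's stated aim, which covers nutritional and clinical outcomes.

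**Working it through.** The protocol gives no expected complication rate or length of stay, so there is no figure of its own to reproduce here. The rates and stays below are assumptions, shown over a range.

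**1. When the median complication count is 0**

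Inputs from Sample size calculation {14}: 28 recruited and 23 evaluable patients per arm.

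Let X be the number of patients in an arm with at least one complication.

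- n = 28: the median is the mean of the 14th and 15th ordered counts. It is 0 only if both are 0, that is, if X ≤ 13.
- n = 23: the median is the 12th ordered count. It is 0 if X ≤ 11.

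In an arm of 28, any result from 0 of 28 up to 13 of 28 (13/28 = 46%) therefore gives a median of 0.

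**2. How likely this is**

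With X ~ Binomial(n, p) and a common rate p, the chance for one arm is P(X ≤ 13) or P(X ≤ 11). For three independent arms it is that value cubed.

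| Assumed rate p | One arm, n = 28 | All three, n = 28 | One arm, n = 23 | All three, n = 23 |
|---|---|---|---|---|
| 20% | 0.9996 | 0.999 | 0.9994 | 0.998 |
| 30% | 0.979 | 0.94 | 0.979 | 0.94 |
| 40% | 0.813 | 0.54 | 0.836 | 0.59 |
| 50% | 0.425 | 0.08 | 0.500 | 0.13 |
| 60% | 0.103 | 0.001 | 0.164 | 0.004 |

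**3. What a real difference would look like**

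Take two arms of 28 with true rates of 10% and 30%. The chance of a zero median is 1.000 (to three decimals) in the first and 0.979 in the second, so both medians are 0 with probability about 1.000 × 0.979 = 0.98. The expected numbers of affected patients are 28 × 0.10 = 2.8 and 28 × 0.30 = 8.4. Observed results of 3 and 8 would be reported as 11% and 29%, but both as median 0.

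**4. Length of stay: the places side by side**

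| Place | Start of the count |
|---|---|
| Table 2, length-of-stay row | admission, labelled V1 |
| Table 2, change outcomes | V1 is baseline |
| Study setting {9} | baseline is at the outpatient clinic; first ward contact is the day before surgery |
| Length of hospital stay, {18a} | day of admission, from hospital records |

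V1 and admission are thus different days, and only the label in the length-of-stay row says otherwise. The end point, 1 day before discharge, is the same in both definitions.

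**5. What the label would do if followed literally**

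Assume supplementation starts at V1 and admission is the day before surgery. Then the V1-to-V3 interval is (preoperative supplement days − 1) + stay.

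- 5 preoperative days add 5 − 1 = 4 days; 14 add 14 − 1 = 13 days.
- For an assumed 5-day stay the interval is 9 to 18 days, of which 4/9 = 44% to 13/18 = 72% is waiting.
- Over assumed stays of 3 to 10 days, the waiting share runs from 4/14 = 29% to 13/16 = 81%.

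This shows only what the wrong label could cost. It does not show that the count will be made this way.

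**The case against.** **Counts and percentages are already promised.** The outcome text names a rate, and {20a} reports categorical data as counts and percentages. On those statements 10% and 30% would both be visible, and a summary column does not fix the between-group test. This stands as a limit: the median is not certain to be what is reported. But Table 2 is where the protocol specifies the summary for each outcome, and its entry conflicts with the other two places.

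**The zero median is conditional.** A reader might infer that complications will be 0 in every arm. The documents do not support that as a fact, because they give no complication rate and the result fails at rates of about 50% or more.

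**Length of stay is defined well enough.** A reader might infer that this outcome measures waiting time. The row itself speaks of hospitalisation and admission, and {18a} starts at the admission day from hospital records. Even the literal V1 interval would mix waiting with stay. This objection stands: a wrong label is the likelier explanation.

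**A difference between arms is not shown.** A reader might infer that the added time would be longer in the two groups with preoperative supplement, since the usual-care group has no stated preoperative minimum. But patients are already scheduled for surgery when they become eligible, allocation follows enrolment, and nothing says that surgery is moved to fit the supplement. The Dietary intake subsection asks for food records two weeks before surgery without distinguishing arms. This objection also stands.

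**Conclusion.** Both Table 2 defects are in the text, but they differ in weight.

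The complications entry matters more. It states a summary that conflicts with the named outcome and with {20a}. If the rate is up to about 30%, it would very probably show 0 in all three arms of 28 (probability 0.94 at 30%, above 0.99 at 20%). At 40% the probability is 0.54 and at 50% it is 0.08. These figures assume a common rate in all arms, independent patients and 28 per arm; 23 per arm changes little.

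The V1 label is an inconsistency to correct, not evidence that length of stay will be measured wrongly. Nor do the documents support the stronger inference that these outcomes would show nothing whatever the supplement does, since {20a} and {18a} both contain usable definitions.

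Both outcomes are secondary. The sample size, which rests on serum albumin, and the primary outcomes are not affected.

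**What to change.** 1. **Complications row of Table 2:** replace Median with the number and percentage of patients with at least one complication, for any and for major complications. Count cumulatively within 30 and within 90 days of surgery, which also settles whether the table's visit-based wording means cumulative or interval counts. Compare arms as proportions, for example by a risk difference with a 95% confidence interval.
2. **Length-of-stay row of Table 2:** delete the V1 label, so that the count starts at the day of hospital admission in the hospital records, as in {18a}. The end point needs no change, because both places agree on it.

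The cost is an edit to two table rows. The data are already planned for collection and the sample size does not change. The protocol plans no analysis before study completion and describes enrolment as active, so the correction can be made and dated before any comparison between arms.

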### Participant timeline {13}

Participant timeline is shown in Tables 1 and 2

### Sample size calculation {14}

The sample size required is calculated based on the improvement in serum albumin level. To detect a between-group difference of at least 4g/L of serum albumin level that would cause approximately 25% reduction in morbidity among patients who have serum albumin in the normal range (around 38 g/L) [36], and a standard deviation of 6.5g/L, at 80% power and with a 5% alpha error. A minimum of 23 subjects per group is required. After accounting for a 20% drop-out rate, 28 subjects are required per group and thus a total of 84 subjects will be recruited in the three groups.

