## Assignment of interventions: allocation

### Randomisation {16a}

This is an open-labelled study and randomisation is performed using computer-generated software [37] by personnel not involved in the data collection. Patients are randomised into one of the three intervention arms in the ratio of 1:1:1 without stratification by study sites. The randomisation is done through the block method whereby the block size is either 3, 6, or 9 to minimise predictability and selection bias.

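### The stated between-group albumin inputs require 42 to 43 evaluable patients per group (two-sided), not 23, so the 80% power claim is unsupported as written

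*Protocol article*

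**What the plan says.** All of the sizing is in the protocol article, Sample size calculation {14}. The basis is serum albumin: "The sample size required is calculated based on the improvement in serum albumin level". The target is "To detect a between-group difference of at least 4g/L of serum albumin level", with "a standard deviation of 6.5g/L", "at 80% power and with a 5% alpha error". The result is "A minimum of 23 subjects per group is required". Attrition is then added: "After accounting for a 20% drop-out rate, 28 subjects are required per group", which makes 84 over three groups.

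The section does not name the test or formula, the sidedness, any baseline adjustment or any within-patient correlation. It also does not say whether 6.5 g/L is the SD of a single albumin value or of a change.

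The design is parallel-group. Under Randomisation {16a}: "Patients are randomised into one of the three intervention arms in the ratio of 1:1:1". Statistical methods {20a} makes a repeated measures ANOVA (time by group) the primary analysis, on a per-protocol complete-case set, and makes ANCOVA secondary.

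**The concern.** Every input is printed, so the figure can be checked, and it fails for the comparison the section describes. A difference between two independent groups carries sampling error from both groups. The number given is about half of what that comparison needs.

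Serum albumin is one of four primary outcomes and the only one with a power statement. The section ties 4 g/L to a reduction in morbidity of roughly a quarter, so the protocol itself treats that difference as worth detecting. If the power for it is well below 80%, a non-significant albumin result says much less about a 4 g/L effect than a reader of the section would suppose.

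**Working it through.** **Inputs** (Sample size calculation {14}): difference 4 g/L, SD 6.5 g/L, power 80%, alpha 5%. Standardised difference d = 4/6.5 = 0.615, so d² = 0.379. Sidedness is not stated; two-sided is assumed and one-sided is also shown.

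**1. Trying to reproduce 23.**

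| Calculation | n per group |
|---|---|
| Two groups, two-sided, normal: 2 × (1.960 + 0.842)² / d² = 2 × 7.849 / 0.379 = 41.5 | 42 |
| Two groups, two-sided, exact t: 42.4 | 43 |
| Two groups, one-sided, normal: 2 × (1.645 + 0.842)² / d² = 32.7 | 33 |
| Two groups, one-sided, exact t: 33.3 | 34 |
| Three-group one-way ANOVA, means 0, 0, 4 | 40 |
| Three-group one-way ANOVA, means 0, 2, 4 | 52 |
| One-sample or paired t, two-sided: 22.7 | 23 |

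No unadjusted between-group calculation with a 4 g/L difference comes near 23. The one-sample or paired t-test with d = 0.615 gives 23 exactly (power 78.6% at 22 and 80.5% at 23). That formula applies to a mean change within one group, not to a difference between groups.

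**2. Power of an unadjusted pairwise t-test for 4 g/L**, from the noncentral t with 2n − 2 degrees of freedom and noncentrality d√(n/2).

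| n per group | Two-sided | One-sided |
|---|---|---|
| 22 | 51.4% | 64.2% |
| 23 | 53.2% | 65.9% |
| 28 (nobody lost) | 61.8% | 73.5% |

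With 23 per group, 80% two-sided power is reached at a difference of 5.5 g/L. Alternatively, 4 g/L would have 80% power if the SD were about 4.7 g/L.

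**3. Meaning of the SD.** If 6.5 g/L is the SD of the change in albumin, the calculation in step 1 is unchanged and still gives 42 to 43. If it is the SD of a single value, a change score has variance 2(1 − r) × 6.5², and 23 per group reaches 80% only with r of about 0.73.

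**4. Baseline-adjusted ANCOVA.** The residual SD is 6.5 × √(1 − r²). At r = 0.5 this is 5.63 g/L, and 23 per group gives about 65% power. Reaching 80% at 23 needs r of about 0.69. The protocol states no r.

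**5. Drop-out step.** 23/0.8 = 28.75, so 29 per group and 87 in total. The stated 28 leaves 28 × 0.8 = 22.4, about 22 evaluable and below the stated minimum of 23. The figure 28 agrees with 23 × 1.2 = 27.6 rounded up. The effect on power is small: 51% at 22 against 53% at 23.

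**The case against.** The best defence is that an unadjusted single-time-point t-test is not what the trial plans. Statistical methods {20a} uses repeated measures ANOVA first and ANCOVA second, and both can be more efficient. Numbers near 23 can be reached that way: ANCOVA with r of about 0.69, change scores with r of about 0.73, or an average over three visits with a between-visit correlation of 0.3 (assuming equal correlations), which needs 24 per group for two groups.

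Part of this stands, and it limits the point. Three stronger readings are tempting but are not supported:

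- A reader might infer that 23 was certainly, or could only have been, produced by a one-sample or paired formula. The section names no formula. The exact match makes that origin likely, but the adjusted routes above also land at or close to 23.
- A reader might infer that the trial's power is 53%, and that a true 4 g/L effect would be missed nearly half the time. That holds for an unadjusted two-sided pairwise comparison. The power of the planned time-by-group test depends on the pattern over visits and on the correlation, neither of which is given. Splitting alpha over three pairwise comparisons would lower the figure further, but {20a} uses 0.05 throughout, so no such loss belongs in the size of this error.
- A reader might infer that a null result will be reported as showing no benefit. The protocol contains no such rule.

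The defence does not rescue the section. Each adjusted route needs a correlation that is neither stated nor justified, and one-sided testing still needs 33 to 34.

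**Conclusion.** The sample size section is wrong as written. Its own between-group inputs require 42 to 43 evaluable patients per group two-sided, against 23 stated. With 20% drop-out that would be 42/0.8 = 52.5, so 53, or 43/0.8 = 53.75, so 54 per group, against 28 planned. The claim of 80% power for 4 g/L is therefore unsupported by the information given. For an unadjusted two-sided pairwise comparison, power is about 53% at 23 per group.

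This rests on reading the target as a difference between two independent groups, which is what the section says, and on taking 6.5 g/L as the SD of the quantity compared. The 53% also assumes a two-sided 5% test without adjustment. How the sponsor arrived at 23 remains unknown. The drop-out slip is real but minor, at one patient per group.

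**What to change.** Restate Sample size calculation {14}:

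- Name the test, the sidedness, and whether 6.5 g/L is the SD of a single albumin value or of a change.
- State that 23 evaluable patients per group give about 53% power for 4 g/L, or 80% power for about 5.5 g/L, in an unadjusted two-sided pairwise comparison (62% for 4 g/L if all 28 are evaluable).
- If the sizing relied on a baseline or repeated-measures correlation, state its value, justify it and give the resulting power for the analysis it belongs to. An ANCOVA with r = 0.5, for example, gives about 65%.
- Commit to reporting between-group albumin differences with 95% confidence intervals read against 4 g/L, and say that a non-significant result does not by itself exclude 4 g/L.
- Correct the drop-out step to 29 per group (87 in total), or keep 28 and say that this leaves about 22 evaluable.

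The cost is wording, plus a less favourable power statement unless a correlation can be justified. The restatement requires no additional enrolment, which matters because the Trial status section reports recruitment already under way. Choosing 29 rather than 28 per group would add three patients in total and is optional.

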### Recruitment {15}

The patients are recruited based on the referral from the doctors in charge or acquired from the clinic appointment list after confirmation of cancer diagnosis and elective surgery. All patients are provided study information with detailed explanation by graduate research assistant and to return written informed consent prior to screening for eligibility.

## Assignment of interventions: allocation

### Randomisation {16a}

This is an open-labelled study and randomisation is performed using computer-generated software [37] by personnel not involved in the data collection. Patients are randomised into one of the three intervention arms in the ratio of 1:1:1 without stratification by study sites. The randomisation is done through the block method whereby the block size is either 3, 6, or 9 to minimise predictability and selection bias.

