### Study design {8}

This study is a multi-centre, open-label, multi-arm, parallel-group randomised controlled trial at two tertiary hospitals. This protocol is written in accordance with the Standard Protocol Items: Recommendations for Interventional Trials (SPIRIT) checklist. The schedule of enrolment, interventions, and assessments for the duration of the study is tabulated in Table 1. Patients enrolled in the study are randomised into 3 arms and followed up at baseline, a day prior to surgery, a day prior to discharge, 30 days after surgery, and 90 days after surgery (Fig. 1).

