### Participants and eligibility criteria {10}

Potential patients are acquired through assessing the registry of surgical clinics and direct referrals from the doctors at the clinics. Patients are eligible if he or she meets the following criteria: male or female from all ethnicity, aged between 25 and 65 years, diagnosed with breast or colorectal cancer and scheduled for elective surgery, BMI not less than 18.0 kg/m^2^, stabilised comorbidities based on the A.S.A Physical Status Classification System Class 1 and 2 [33], and met at least two characteristics of A.N.D/A.S.P.E.N diagnosis of malnutrition, i.e., insufficient energy intake, weight loss, loss of muscle mass, loss of subcutaneous fat, localised or generalised fluid accumulation, and diminished functional status as measured by handgrip strength [34]. Patients who require enteral or parenteral feeding; are currently pregnant or lactating; currently on chemotherapy or radiotherapy; have done total gastrectomy or ileostomy; are diagnosed with metastasised cancer, upper gastrointestinal cancer, terminal diseases, decompensated liver or renal disease, dementia, and the major concurrent metabolic problem such as uncontrolled diabetes; and are currently on regular steroids prescription are excluded. Patients involved in the Enhanced Recovery After Surgery (ERAS) protocol will not be recruited into this study.

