#### Postoperative complications

The postoperative complications are defined as any deviation from the normal postoperative course and divided into minor and major complications. Minor complications include minor risk events, such as wound infection, urinary tract infection, or postoperative ileus [43]. Major complications include potentially life-threatening complications and those with a need of surgical, endoscopic, or radiological intervention, such as an anastomotic leak, abdominal abscess, and pneumonia [43]. Any readmission to the hospital for 30 and 90 days after surgery is to be recorded including the length of hospital stay and reason of readmission.

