## Statistical methods

### Statistical methods for primary and secondary outcomes {20a}

Statistical analyses will be performed using the Statistical Package for the Social Science software (SPSS version 26, IBM, USA). The normality of the data will be evaluated using Shapiro-Wilk’s test. Normally distributed data will be expressed as mean and standard deviation. Skewed data will be described using median with interquartile range for skewed data. Categorical data will be expressed in count and percentages. Evaluation of outcomes will be carried out by both intention-to-treat and per-protocol analyses. The primary analysis will take a per protocol approach and the secondary analysis an intention-to-treat (ITT) approach. The per protocol analysis will include patients who fully completed the intervention allocated and attended all visits (‘complete cases’ approach). The primary analysis will employ repeated measures ANOVA (RMANOVA) to assess for time × group interactions. A secondary analysis of difference between groups for continuous variables will be conducted by using analysis of covariance (ANCOVA), controlling for baseline or at discharge values. The ITT approach will include all patients who are randomised to the three groups, irrespective of dropouts. In order to perform RMANOVA using the ITT approach, missing data will be imputed with the last observation carried forward method using the last available data point from the patients. ANCOVA will be restricted to per-protocol basis. *P*-value <0.05 is considered statistically significant for all tests.

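### Cancer type is neither a stratification factor nor a model term, which gives up some precision and leaves chance imbalance in case mix uncorrected

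*Protocol article*

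**What the plan says.** All references are to the Protocol article. Eligible patients are those "diagnosed with breast or colorectal cancer and scheduled for elective surgery" (Participants and eligibility criteria {10}), in a "parallel-group randomised controlled trial at two tertiary hospitals" (Study design {8}). The expected split between the two cancers is not given.

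Allocation is "in the ratio of 1:1:1 without stratification by study sites" (Randomisation {16a}), and the section names no other stratification factor. The "block size is either 3, 6, or 9 to minimise predictability and selection bias"; such blocks balance arm totals but not the cancer mix within arms.

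Statistical methods {20a} makes a per-protocol, complete-case repeated measures ANOVA (RMANOVA) of time by group the primary analysis. The secondary analysis is "analysis of covariance (ANCOVA), controlling for baseline or at discharge values". Neither model has a term for cancer type or hospital, and the section on additional analyses {20b} plans none.

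**The concern.** Cancer type is known for every patient before randomisation and could plausibly affect recovery. The protocol's own text points that way. Its examples of major complications, "such as an anastomotic leak, abdominal abscess, and pneumonia", include two tied to bowel or abdominal surgery, and ileus appears among the minor ones. The other three examples (wound infection, urinary tract infection, pneumonia) are not specific to either operation.

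The change-from-visit outcomes and the ANCOVA covariate deal with differences in starting level. They do not deal with a different course after surgery. If the course differs by cancer type, that variation stays in the residual, and an arm that happens to receive more colorectal patients is compared without correction. Complications and length of stay, also pooled over both cancers, have the same exposure.

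Timing matters too. The trial is open-label and the unblinded investigators analyse it ({17a}), so a cancer-type adjustment introduced after an imbalance has been seen would be hard to defend. The same adjustment specified now is not open to that charge.

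**Working it through.** **Inputs from the article** (Sample size calculation {14}): "To detect a between-group difference of at least 4g/L of serum albumin level"; "a standard deviation of 6.5g/L", with no statement of whether this is the SD of level or of change; 80% power; 5% alpha; 23 evaluable and 28 recruited per arm.

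**Assumptions:** a 50:50 mix of cancers; 6.5 g/L as the total SD of the analysed albumin change; a mean difference D between cancers in that change of 2, 4 or 6 g/L; a two-sided test.

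**1. The plan's own figure.** For two independent groups, n = 2(1.960 + 0.842)² × 6.5² / 4² = 2 × 7.85 × 42.25 / 16 = 41.5, so 42 per group, not 23. A paired or one-sample t calculation does return 23. That is a separate matter. It is relevant here only because power for 4 g/L starts at about 62% with 28 per arm and 53% with 23, not at 80%.

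**2. Size of chance imbalance.** The SD of the difference in colorectal share between two arms is √(2p(1−p)/n).
- n = 28, p = 0.5: √(0.5/28) = 0.134; × 1.96 = 0.262, or ±26 points.
- n = 28, p = 0.3: √(0.42/28) = 0.122; × 1.96 = 0.240, or ±24 points.
- n = 23, p = 0.5: √(0.5/23) = 0.147; × 1.96 = 0.289, or ±29 points.

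In 400,000 simulated allocations (28 per arm, 50:50), the absolute difference had median 11 points and 95th percentile 25 points (7 patients in 28). A given pair of arms differed by 20 points or more in 14% of allocations, and at least one of the three pairs did in 30%.

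**3. Shift and power.** Shift = imbalance × D. Share of variance due to cancer type = D² × 0.25 / 6.5². Power for a 4 g/L effect is from 20,000 simulated two-arm trials per setting, without and then with a cancer-type covariate.

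| D (g/L) | Variance share | Shift at 25 points | % of 4 g/L | Power, 28 per arm | Power, 23 per arm |
|---|---|---|---|---|---|
| 2 | 0.024 | 0.5 g/L | 13% | 62% → 62% | 54% → 54% |
| 4 | 0.095 | 1.0 g/L | 25% | 62% → 66% | 53% → 56% |
| 6 | 0.213 | 1.5 g/L | 38% | 62% → 72% | 53% → 62% |

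At the median imbalance the shift is only 0.107 × 2 = 0.2 g/L to 0.107 × 6 = 0.6 g/L. With 23 completers per arm, the 95th-percentile shift is 0.6, 1.2 and 1.8 g/L for D = 2, 4 and 6.

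**4. Type I error.** Averaged over allocations, the simulated two-sided rate was 4.7% to 5.2%, with or without the covariate. Given an imbalance at the 26-point limit, the unadjusted test is off-centre. The rejection threshold is 1.96 × 6.5 × √(2/28) = 1.96 × 1.74 = 3.40 g/L.
- D = 4: shift 1.05; residual SD √(42.25 − 4) = 6.18, so SE 1.65. The upper tail beyond (3.40 − 1.05)/1.65 = 1.42 and the small lower tail total about 8%.
- D = 6: shift 1.57; residual SD √(42.25 − 9) = 5.77, so SE 1.54. The tails total about 12%.

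The simulation treats a single change value in two arms. It stands in for the ANCOVA or for one contrast of the RMANOVA, not for the full repeated measures model.

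**The case against.** Unstratified blocked randomisation of 84 patients is valid. Chance imbalance is part of sampling error: variation between cancers already sits in the SD, and so in the standard error of 1.74 g/L, and step 4 confirms that the overall error rate holds at about 5%. Differences in stable albumin level are largely removed by the change outcomes and the ANCOVA covariate. The article gives no difference in postoperative course, and at 2 g/L adjustment gains nothing. A statistical analysis plan that is not shown might also add the factor.

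Most of this stands. It rules out describing the omission as bias or invalidity, and it makes the gain conditional on D. It does not remove the point. The article goes further than leaving the model open: it names the models and the one covariate. The same step 4 shows that, once a large imbalance has occurred, the unadjusted test is miscalibrated for the trial in hand.

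The objection is strongest on hospital. The article offers neither a figure nor a mechanism for a hospital effect, so hospital can be at most an optional second factor.

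**Conclusion.** The point holds as one of efficiency and pre-specification. Cancer type is absent from both the allocation and the stated models. Under a 50:50 mix, 28 per arm and an assumed difference of 2 to 6 g/L, an imbalance near the 95% limit moves the albumin contrast by 13% to 38% of the target. Adjustment is worth between nothing and ten points of power. All of these sizes depend on D and the case mix, neither of which the article gives.

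A reader might infer that imbalance could create or hide most of the 4 g/L effect, or that the test is invalid. The documents do not support either reading. The chance that a given pair shifts by 2 g/L, half the target, is 0.02% at D = 4 and 1.0% at D = 6. For the 95th-percentile shift to reach half the target, cancer type alone would need to account for about 8 g/L, and nothing in the article suggests a difference of that size. Overall type I error is unaffected.

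**What to change.** In Statistical methods {20a}, pre-specify the following:
- **ANCOVA:** cancer type (breast or colorectal) as a fixed factor beside the earlier value of the outcome.
- **RMANOVA:** cancer type and its interaction with time. A main effect alone does not sharpen the time by group test.
- **Complications and length of stay:** comparisons stratified by cancer type, for example Mantel-Haenszel for complications and a stratified rank test for length of stay. The article names no specific model for complications, so this adds a method.
- **Hospital:** optional as a second additive factor. A full arm by cancer by hospital factorial should be avoided, because 84 / 12 leaves only 7 patients per cell on average.

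The randomisation list stays as it is, and no new data are needed. The cost is one degree of freedom per factor in the ANCOVA, and visits minus one per factor-by-time term in the RMANOVA (four if all five visits are used). There is little or no gain if the two cancers follow a similar course.
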